**Figure 1 figure1:**
[figure not shown]
Participant flow chart. SMART: Self-Management and Recovery Training.

**Table 2 table2:** Schedule of data collection.

Data collection method/instrument			Baseline		Daily		Weekly		2-week follow-up		2-month follow-up	
**SMART^a^ Recovery participants**												
	**Smart Track app**											
		Data analytics				✓						
		ROM items^b^						✓				
	**Telephone interview**											
	Demographics			✓								✓
	**Network of Alcohol and other Drug Agencies Client Outcome Management System**											
		Severity of Dependence Scale		✓								✓
		Drug and alcohol use		✓								✓
		Kessler 10+ scale		✓								✓
		The World Health Organization Quality of Life–8		✓								✓
		New South Wales minimum data set items (living arrangements and income)		✓								✓
		BTOM-C^c^ items on arrests		✓								✓
		BTOM-C items on risky drug using practices		✓								✓
	Substance Use Recovery Evaluator			✓								✓
	Client Services Receipt Inventory			✓								✓
	Mobile App Rating Scale–user version									✓		
	Digital Working Alliance Inventory									✓		✓
	Qualitative interview (n=20)											✓
**SMART Recovery facilitators**												
	Demographics											✓
	Mobile App Rating Scale–user version											✓
	Qualitative interview (n=10)											✓

^a^SMART: Self-Management and Recovery Training.

^b^See Multimedia Appendix 2 for a detailed description of routine outcome monitoring items as a function of assessment domain and frequency of administration.

^c^BTOM-C: Brief Treatment Outcome Measure-Concise.

### Data Handling and Storage

Initially, the ROM data entered by participants into Smart Track will be stored locally on the participants’ phones. When the participants connect to the internet, ROM data will be transmitted to a secure mobile and web app development platform (managed by SRAU), before transmitting to a secure server hosted by the University of Wollongong.

The participants’ responses to the baseline and follow-up research assessment instruments will be entered at the time of interview directly into REDCap, a secure web application for building and managing online surveys and databases. Further information about data management, monitoring, and dissemination is provided in Multimedia Appendix 3.

### Key Measures and Assessment Instruments

#### Primary Objectives: Feasibility and Acceptability

##### Mobile App Data Analytics

Mobile app data analytics will be captured daily throughout the study period using a mobile and web app development platform. Mobile app data analytics provide insight into how and when participants interact with an app (including participants’ interactions with the on-site tablets provided by the research team). In this study, analytics will be used to inform both feasibility (primary objective) and to describe usage patterns (secondary objective).

##### Qualitative Feedback

A qualitative evaluation (described under *Nested Qualitative Evaluation*) will be conducted 2 months postbaseline to collect detailed feedback from study participants and facilitators regarding their experience of and satisfaction with Smart Track.

##### App Quality Assessment

The Mobile App Rating Scale (MARS) [52] is designed to assess the quality of mHealth apps. The original version of this rating tool is designed to be completed by researchers, professionals, and/or clinicians [52]. The Mobile Application Rating Scale–User Version (uMARS [53]) is a simplified, end-user version. A total of 16 items are used to assess app quality across 4 domains (engagement, functionality, aesthetics, and information quality). Items are rated on a scale from 1 to 5 (1=*inadequate* and 5=*excellent*). Means are calculated for each quality domain and summed to produce an overall app quality mean score. Each instrument also contains 4 additional items to assess *subjective quality* and a further 6 items to assess the perceived impact of the app. Both the MARS [52] and uMARS [53] have excellent internal consistency and sound test-retest reliability.

The Digital Working Alliance Inventory (D-WAI) [54] is a brief, simple scale designed to assess therapeutic alliances within the context of app usage. It was recently developed to address the need for improved assessment of working alliances when evaluating the quality of digital health apps [54]. The D-WAI comprises 6 items and is derived from the short form of the Working Alliance Inventory [55], a commonly implemented and validated index of working alliances [56-58].

##### Cost Analysis

###### Health Services and Medication: Usage and Cost

An adapted version of the Client Service Receipt Inventory (CSRI)—*generic* UK mental health [59] will be used to assess health services and medication usage. The content of this inventory has been updated to reflect key sources of mental health expenditure in Australia [60]. These data will allow us to explore clinical and treatment characteristics that may be associated with app usage and will provide some insight into costing.

###### Time and Resource Utilization

Time and resource utilization will be captured in Microsoft Excel using a *cost capture template* [61-63]. This template will be used by the research team to maintain a record of cost data associated with the conduct of the study and the development and implementation of Smart Track. Only costs required to develop and implement the Smart Track app will be included in the cost analysis.

#### Secondary Objectives

##### Usage Patterns, Psychometric Properties, and Participant-Reported Outcomes

Secondary objectives will be informed by (1) participant-entered (and missing) data for Smart Track ROM items (detailed in Multimedia Appendix 2), (2) app-generated data analytics, and (3) the following data (eg sociodemographic characteristics; drug and alcohol use; health and social functioning; and recovery) collected by the research team at baseline and follow-up assessments.

##### Demographic Characteristics

Collection of sociodemographic characteristics (referral source, date of birth, gender, marital status, indigenous status, education/training, accommodation, and income) will be guided by items from the CSRI [59] and/or NSW minimum data set (MDS) for drug and alcohol treatment services [64].

The Network of Alcohol and other Drug Agencies (NADA) Client Outcome Management System (COMS) was developed by NADA to address the need for greater consistency in how outcomes are assessed across the drug and alcohol treatment sector [46]. We have chosen to use the COMS in this study to ensure that our data are directly comparable with the broader drug and alcohol treatment sectors. The COMS comprises a battery of items designed to assess 4 key domains: (1) drug and alcohol use, (2) psychological health, (3) health and social functioning, and (4) blood-borne virus (BBV) risk. The instruments used to assess each domain are outlined below. The COMS will be administered in full at baseline and at 2-month follow-up. A subset of items (Multimedia Appendix 2) will also be administered via Smart Track.

###### Client Outcome Management System: Drug and Alcohol Use

####### Severity of Dependence Scale

The Severity of Dependence Scale [65] is a 5-item screening measure of the psychological aspects of dependence that takes less than 1 min to complete. The items assess feelings of impaired control over drug taking, together with preoccupations and anxieties about drug taking. Participants will be asked to respond based on the substance that was causing them the greatest concern (1) over the preceding 2 months and (2) when they began attending SMART Recovery. The items are rated on a 4-point Likert scale, and total scores range from 0 to 15. Higher scores indicate a higher level of dependence. It is widely validated for use across a range of drug types, including heroin, cannabis, cocaine, amphetamine, and benzodiazepines [65-67].

####### Substance Use

Alcohol and tobacco use is measured by assessing both frequency (number of days) and quantity used during the preceding 4 weeks. Furthermore, 2 separate measurements for alcohol are included: number of days the person drank alcohol (and average number of drinks per day) and number of days of heavier drinking than usual (and average number of drinks on those days). For benzodiazepines and any illicit drugs, only the number of days of use is assessed.

###### Client Outcome Management System: Psychological Health

The Kessler 10 scale (K10) [68] is a widely used self-report measure of psychological distress. It comprises 10 questions that assess the level of nervousness, agitation, psychological fatigue, and depression in the past 4 weeks [68]. Each item is scored from 1 to 5, from *none of the time* to *all of the time*. Scores are then totaled, resulting in a K10 score between 10 and 50, with higher scores indicating greater distress [69]. The Kessler 10+ scale includes 4 additional questions to provide a context for interpretation (number of days where work, study, and/or management of daily activities were stopped and/or reduced because of these feelings; number of times professional help was sought; and perceived contribution of physical health problems to reported distress) [46]. The K10 has been successfully used in a range of populations, including a range of different Australian settings [69] and specifically with users of AOD in Australian settings [70].

###### Client Outcome Management System: Health and Social Functioning

####### World Health Organization Quality of Life Scale–8

The World Health Organization Quality of Life–8 [71] questions (also known as the EUROHIS QoL-8) is a very brief adaptation of the WHOQOL-100 and the WHOQOLBREF. Each item is scored from 1 (eg, not at all/very poor/very dissatisfied) to 5 (eg, completely/very good/very satisfied). Items are totaled (range 8-40), with higher scores reflecting greater perceived quality of life over the preceding 2 weeks. Domain scores can also be calculated for overall perception of the quality of life, overall perception of health, physical quality of life, psychological quality of life, satisfaction with social relationships, and satisfaction with the environment. It has been used and validated across a range of populations and settings [45,71], including AOD [72] and mental health [73].

####### New South Wales Minimum Data Set Items

To provide a differing and more objective assessment of the changes in the perceived quality of life [46], the COMS also includes two items on living arrangements (“Who do you live with?” and “Usual accommodation?”) and 1 item on income status (“What is your main source of income?”) taken from the NSW MDS [64]. Each item is answered by selecting one option from the response categories provided.

Two items on crime from the Brief Treatment Outcome Measure–Concise (BTOM-C) [47] are also included. These items were developed by the NSW Ministry of Health and assess the number of times the individual has been arrested in the last 2 months and how many arrests were for offenses committed in the preceding 2 months.

###### Client Outcome Management System: Blood-Borne Virus Risk

The BBV exposure risk-taking domain of the COMS comprises 4 items from the BTOM-C [47] on injecting drug use and overdose. These items are part of the validated BTOM measurement tool developed by NSW Health [47]. They are designed to measure changes and outcomes in relation to injecting and other risky drug use practices.

##### Client Perspectives of Recovery

The Substance Use Recovery Evaluator (SURE) [43] is designed to measure recovery from drug and alcohol dependence. It was developed in close consultation with people in recovery and comprises 21 items across 5 domains (drinking and drug use, self-care, relationships, material resources, and outlook on life). Items are summed to generate domain scores and an overall recovery score, with higher scores indicating greater progress toward recovery. Evidence supports face and content validity, acceptability, and usability for people in recovery [43]. We have selected the SURE as it is the first patient-reported outcome measure to provide a multidomain assessment of recovery, as defined by adults with experience of addiction [19]. Holistic assessment across a range of domains is consistent with both service user needs [74] and recovery-oriented service provision [19], thereby increasing the relevance of our findings to both service users and service providers. The SURE will be administered in full at baseline and at 2-month follow-up, with items also administered via Smart Track.

##### Nested Qualitative Evaluation

Qualitative interviews will be conducted 2 months postbaseline to explore the experience and opinions of participants with diverse engagement with Smart Track. Participants will be purposively sampled according to their baseline characteristics, pattern of Smart Track usage, and responses to the 2-month follow-up assessment. Specifically, we wish to explore the experience and opinions of 2 groups of SMART Recovery participants: (1) those who attended SMART groups regularly and completed the ROM regularly (n=10) and (2) those who attended SMART groups regularly and did not complete the ROM regularly (n=10). A qualitative researcher independent from the research team will use a topic guide to ask additional open-ended questions to the selection of participants (n=20) until the nominated sample size in both groups is reached. The research team will monitor recruitment to ensure that there is an adequate distribution of gender, main behavior of concern, geographical location, and group setting. Two corresponding groups of SMART Recovery facilitators (n=5 for each group) will also be recruited, namely (1) one group with members who regularly used Smart Track and (2) another group with members who did not regularly use Smart Track.

All interviews will be audio-recorded. A professional transcriber working under a confidentiality agreement will transcribe the recordings. The transcripts will be checked against the recordings for accuracy and deidentified (by removal of identifying information).

### Study Outcomes

Primary and secondary endpoints are presented in Tables 3 and 4, respectively.

**Table 3 table3:** Primary endpoints.

Primary objective	Primary endpoint
To explore the feasibility of using Smart Track as part of SMART^a^ Recovery groups for the purposes of ROM^b^ and tailored feedback	Proportion of eligible participants who consent to the study Proportion of missing data for each of the ROM items/instruments at each week of administration, across the 2-month period of Smart Track usage Costs associated with developing Smart Track and maintaining the app until the completion of data collection Participant engagement with Smart Track, as indexed by data analytics captured daily across the data collection period
To explore the acceptability of using Smart Track as part of SMART Recovery groups for the purposes of ROM and tailored feedback	Detailed qualitative feedback from SMART Recovery group members and facilitators to explore their experience of and satisfaction with Smart Track (2-month follow-up) Quality ratings as assessed by participant and facilitator ratings of the user version of the Mobile App Rating Scale (2-week follow-up) and Mobile App Rating Scale (2-month follow-up), respectively Digital therapeutic alliance ratings as assessed by participant ratings of the Digital Working Alliance Inventory (2-week and 2-month follow-up)

^a^SMART: Self-Management and Recovery Training.

^b^ROM: routine outcome monitoring.

**Table 4 table4:** Secondary endpoints.

Secondary objective	Secondary endpoints
To explore how participants engage with the app and describe usage patterns	Demographic, clinical, and treatment factors (as measured by Client Service Receipt Inventory, COMS^a^, and SURE^b^ at baseline and 2-month follow-up) associated with (in)completion of Smart Track ROM^c^ items Data analytics captured daily across the data collection period
To provide preliminary evidence for the psychometric properties of the ROM items administered by Smart Track	Internal reliability and convergent and divergent validity of COMS and SURE items administered by Smart Track (relative to the complete versions administered at baseline and 2-month follow-up)
To provide preliminary evidence for participant-reported outcomes in behaviors of concern, recovery, and mental health	Participant-reported progress across the 2-month period of app usage in the following: Addictive behaviors (COMS [41] and item adapted from the Screener for Substance and Behavioral Addictions [42]) Addiction recovery (SURE [43]) Mental health (Kessler [44,68])

^a^COMS: Client Outcome Management System.

^b^SURE: Substance Use Recovery Evaluator.

^c^ROM: routine outcome monitoring.

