**Conclusions:**

To the best of our knowledge, this study is the first to use ROM and tailored feedback within a mutual support group setting for addictive behaviors. Our study design will provide an opportunity to identify the acceptability of a novel mHealth ROM and feedback app within this setting and provide detailed information on what factors promote or hinder ROM usage within this context. This project aims to offer a new tool, should Smart Track prove feasible and acceptable, that service providers, policy makers, and researchers could use in the future to understand the impact of SMART Recovery groups.

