#### Secondary Objectives

##### App Engagement and Usage Patterns

A detailed exploration of the relationship between app usage (as indexed by frequency of ROM completion, number of missing items, and time to disengagement) and participant characteristics (demographic, clinical, and treatment variables) will be explored using linear regression. Furthermore, we intend to explore the ROM data graphically to see (1) whether it is likely to characterize particular patterns of usage and (2) whether these patterns appear to be influenced by various participant characteristics. Potential patterns that emerge during this exploratory phase will be followed up using latent trajectory analysis. This will clarify whether app use increases, decreases, or has some other pattern over time. Descriptive statistics will also be used to summarize app-generated data analytics.

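### Table 4 lists 2-month CSRI, COMS and SURE values beside baseline values as factors for ROM completion over those same 2 months; associations with the 2-month values cannot be read as influences on usage

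*Protocol article*

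**What the plan says.** Table 4 (Study Outcomes) sets the secondary objective "To explore how participants engage with the app and describe usage patterns". Its first endpoint consists of demographic, clinical and treatment factors, taken from the CSRI, COMS and SURE "at baseline and 2-month follow-up) associated with (in)completion of Smart Track" ROM items. Both time points are named. The section introducing the COMS confirms the schedule: "The COMS will be administered in full at baseline and at 2-month follow-up". The SURE and CSRI follow the same schedule (Client Perspectives of Recovery; Table 2).

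The usage being explained builds up between those two assessments. Table 3 counts missing ROM data "across the 2-month period of Smart Track usage". The analysis section, App Engagement and Usage Patterns, measures usage "as indexed by frequency of ROM completion, number of missing items, and time to disengagement" and says that its relationship with "participant characteristics (demographic, clinical, and treatment variables) will be explored using linear regression". It gives no time point for the characteristics. The same paragraph plans to look at usage patterns graphically and ask "whether these patterns appear to be influenced by various participant characteristics".

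Table 4 also lists progress on the COMS, SURE and Kessler scale over the 2 months of app use as participant-reported outcomes. The Conclusions of the Abstract say that the design will "provide detailed information on what factors promote or hinder ROM usage within this context".

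**The concern.** The same 2-month scores have two roles in Table 4. They are outcomes of the period of app use, and they are factors to be related to how much the app was used in that period. The article's Background gives a reason to expect usage to affect them: it cites evidence that tailored feedback improves treatment outcomes, and the app delivers tailored feedback.

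If people who complete more ROM items recover somewhat more, the 2-month SURE or Kessler score will be associated with completion even when recovery or distress had no bearing on whether they completed the items. Listed among the factors associated with completion, and read in the light of the article's words about influence and about promoting or hindering use, such a result points the wrong way. The Discussion says that the study will inform later intervention studies, and those could then target a consequence of use instead of a cause.

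**Working it through.** The plan states no figure on this point, so there is none to reproduce. The check has two parts.

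**1. Timing.**
- Usage: ROM completion over the 2-month period (Table 3; App Engagement and Usage Patterns).
- Factors: CSRI, COMS and SURE at baseline and at 2 months (Table 4).
- Outcomes: COMS, SURE and Kessler progress over the same 2 months (Table 4).
- Limit on the regression: none stated.

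A baseline value comes before the counted window. A 2-month value is collected at its end, so its association with usage may reflect influence on usage, a consequence of usage, or both. The regression cannot tell these apart.

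**2. Size of a possible misreading.** The inputs are n = 100, the recruitment target under Power, and a two-sided 5% test. The article gives no effect of app use on any score, so that effect is an assumption shown as a range.

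Let U be usage, B the baseline score and F the 2-month score, each with variance 1. Let U be independent of B, and

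F = 0.6·B + b·U + e, with var(e) = 1 − 0.36 − b².

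Then corr(U, B) = 0 and corr(U, F) = b. The 0.6 is also assumed; it does not affect corr(U, F).

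The chance that F is significant, by Fisher's z, is approximately Φ(atanh(b)·√(n − 3) − 1.960), with √97 = 9.849. The opposite tail is negligible for b of 0.2 or more.
- b = 0: 5% by construction.
- b = 0.2: 0.2027 × 9.849 = 1.997; Φ(0.037) = 0.51.
- b = 0.3: 0.3095 × 9.849 = 3.048; Φ(1.088) = 0.86.

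A simulation of simple linear regressions (3,000 trials per row, n = 100) agrees:

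| b | baseline score flagged | 2-month score flagged |
|---|---|---|
| 0 | 5.1% | 5.1% |
| 0.2 | 4.7% | 51.6% |
| 0.3 | 5.5% | 85.3% |
| 0.4 | 4.5% | 99.3% |

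These figures take all 100 participants as followed up. If only 80 were (an assumption), √77 = 8.775 and the Fisher values become Φ(1.779 − 1.960) = 0.43 at b = 0.2 and Φ(2.716 − 1.960) = 0.78 at b = 0.3.

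**The case against.** The strongest reply is that the endpoint claims association only, under an objective to explore and describe. The wording about influence belongs to the graphical look at patterns. The wording about promoting or hindering use describes the whole design, including interviews with regular and irregular completers. On that reading, 51% and 86% are the power to detect a correlation that really exists, not false-positive rates. This stands: the result misleads only when it is read as a driver of usage. But the article invites that reading and does not separate the two sets of values.

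A reader might go further and infer that a 2-month factor cannot influence usage. The documents do not support that. Several follow-up items look back into the usage window: the Severity of Dependence Scale and arrests over 2 months, substance use and the K10 over 4 weeks, and quality of life over 2 weeks. Concomitant care is unrestricted, so relapse, distress or other treatment during the period could affect completion. The direction is ambiguous, not impossible, and such concurrent correlates are worth describing.

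A reader might also infer that follow-up selection biases the association because engaged participants are more likely to attend the 2-month interview. Loss that depends on usage alone does not do this. In simulation with 80% or 60% retention and no true association, 4.5% to 5.9% of trials were flagged, with complete cases or with multiple imputation. Bias appeared only when loss was also made to depend on the 2-month state, which nothing in the article establishes. The plan prescribes multiple imputation for inferential analyses.

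Finally, covariate details may be left to an analysis plan that is not shown. Here, however, the article itself fixes the time points in the endpoint, so this is a stated choice and not an omission.

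**Conclusion.** The point holds as one of timing and interpretation. Table 4 names 2-month values as factors for ROM completion over the preceding 2 months, uses some of the same scores as outcomes, and does not say that only baseline values can bear an explanatory reading. An association with a 2-month value therefore cannot support a statement about what influences, promotes or hinders usage.

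The size depends wholly on an assumed effect of app use. For a characteristic with no influence on usage, the 2-month score would be flagged in about 5%, 51% or 86% of trials at correlations of 0, 0.2 and 0.3 with n = 100, against about 5% for the baseline score. If app use shifts nothing, nothing is distorted. One exploratory secondary endpoint of a single-arm pilot is affected; no primary endpoint or sample-size figure is.

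**What to change.** In App Engagement and Usage Patterns, state that the explanatory variables in the usage models are baseline demographics and baseline CSRI, COMS and SURE values. Amend the first endpoint in Table 4 to match. Report the 2-month values separately, either as participant outcomes or as concurrent correlates of usage (for example, service use during the period), and state that they carry no predictor interpretation.

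The cost is a change of wording in two places and no new data. The small downside is that concurrent correlates leave the explanatory model, although they are still reported. Because the app can be downloaded freely, it would also help to record whether a participant had used it before the baseline assessment; the text shown does not rule this out.
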